### Randomization

After informed consent, patients will be randomized 1:1 into the IG and CG. The randomization will be generated automatically by the ECF after the local ophthalmologist has submitted the patient’s master data (year of birth, sex, and three digits of the zip code) and eligibility criteria in a web-based form. The underlying randomization sequence will be known only to the developers of the ECF (Fraunhofer Institute for Applied Information Technology FIT) who will act independently of the personnel analyzing (Bielefeld University) and conducting (University of Muenster Medical Center) the study. This sequence will be concealed from all study staff so that it cannot be manipulated by physicians, clinical staff, or the patients themselves.

Participants will receive a study identification number after randomization and their assignment to one study group. Owing to the nature of the intervention, it will not be possible to blind either the patients, the personnel conducting the study or the healthcare providers. The independent evaluators of the study will be blinded during the study by being provided solely with a pseudonymized data set for data analysis.

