### Intervention

The main part of the intervention is outpatient monitoring of IOP using a self-tonometer. The glaucoma patients who qualify to participate in the study will be briefed by the local ophthalmologist about the study design as well as the benefits and risks and asked to sign an informed consent form. After randomization, they will be contacted by the Department of Ophthalmology of the University of Muenster Medical Center to arrange an appointment at one of the participating eye hospitals for an initial examination.

The initial examination includes IOP measurement to investigate the pathological pressure peaks, a 30° visual field examination, an OCT of the optic nerve head, a Heidelberg retina tomography (HRT) (if available), and a questionnaire about health-related quality of life. Subsequent to the initial examination, patients will be instructed by the clinical staff in the functioning and handling of the IcareHOME® self-tonometer and 24-h blood pressure measuring device. The patients of the IG will then receive the devices and perform self-tonometry over the course of seven days. They will also undergo initial blood pressure monitoring for 24 h, starting at the end of the training. The IOP and blood pressure values measured will be evaluated by the local ophthalmologists, who can adjust the patient’s therapy on the basis of the results. Thereafter, check-ups will be carried out every 3 months by the local ophthalmologists. The final examination will be performed 12 months after the initial examination at the same participating eye hospital and will replicate the initial one but end with a final interview between the doctor and patient.

All measured values, the medical history, and the imaging performed will be transferred by the local ophthalmologists or hospitals to an electronic case file (ECF), a cloud-based system for the management of the patient’s primary data. The ECF can also be used to raise queries with a glaucoma specialist and senior resident from the University of Muenster Medical Center. IG participants will also have access to the ECF and be able to view all measurement data. The participants will gain a comprehensive insight into their disease progression for the first time and will also become more involved and informed about treatment options.

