Usability	Interviews, questionnaire	During or at end of project						

^***^*Measurement of IOP and blood pressure will be performed either during inpatient stay in participating hospitals (CG) or at home (IG. The blood pressure monitor will be put on in hospital and should be worn at home, while self-tonometry is performed by patients themselves over a time frame of 7 days)*

*Time stamps:*

*T*_*−1*_*:* Enrolment of patients by local ophthalmologists

*T*_*0*_*:* Initial examination in a participating hospital

*T*_*1*_*:* For IG: consultation with local ophthalmologist for evaluation of data from self-tonometry and 24-h blood pressure measurement; for CG: hospital admission for IOP measurements and 24-h blood pressure measurements

*T*_*2*_*:* First check-up examination at a local ophthalmology practice after 3 months

*T*_*3*_*:* Second check-up examination at a local ophthalmology practice after 6 months

*T*_*4*_*:* Third follow-up examination at a local ophthalmology practice after 9 months

*T*_*5*_*:* Final examination in a participating hospital

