### Secondary endpoints

#### Clinical endpoints

Visual field indices such as visual field index (VFI), mean deviation (MD), and pattern standard deviation (PSD) will be determined using standard automated perimetry. These values will be measured on initial and final examination in hospitals and after 9 months during the follow-up visit at the local ophthalmology practice. These measurements will be used to determine the extent of visual field loss due to suspected or confirmed glaucoma. Furthermore, the values will be used to calculate visual field damage and classify stages of glaucoma [20, 21].

RNFL thickness, rim volume, and rim area will be needed to map short- and medium-term results of glaucoma diagnosis and progression within the project time-frame [22]. Those surrogates will be determined with OCT (RNFL thickness) and HRT (rim volume and area), if available, during initial and final examination in participating hospitals.

IOP will be measured on all examinations in participating hospitals and at the local ophthalmology practice. Since low ocular perfusion pressure and low blood pressure are associated with an increased risk of glaucoma, vascular factors can be of importance for further glaucoma treatment planning [23]. Measurement of blood pressure will be performed parallel to IOP monitoring during inpatient stay or at home for 24 h, every 15 min during day between 6 a.m. and 10 p.m. and every 30 min at night between 20 p.m. and 6 a.m.

Health-related quality of life will be evaluated using the EQ-5D-5L questionnaire, a generic multidimensional instrument implemented by the EuroQol Group [24, 25]. The EQ-5D is frequently used to analyze quality of life in ophthalmic diseases such as glaucoma, and glaucoma and disease progression with visual damage are known to influence health-related quality of life [26–29].

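### The reason given for not blinding study personnel does not cover the staff who measure IOP at the 12-month hospital examination, so that secondary endpoint is left open to avoidable observer bias

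*Protocol article*

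**What the plan says.** The Randomization section gives the nature of the intervention as the reason why "it will not be possible to blind either the patients, the personnel conducting the study or the healthcare providers". The only blinded party is the analysis group: "The independent evaluators of the study will be blinded during the study by being provided solely with a pseudonymized data set for data analysis".

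The Intervention section places the final examination 12 months after the initial one, "at the same participating eye hospital and will replicate the initial one but end with a final interview between the doctor and patient". On the examination being repeated it says: "The initial examination includes IOP measurement to investigate the pathological pressure peaks". The other components are a 30° visual field, OCT, HRT where available, and a quality-of-life questionnaire. The legend to Table 2 defines T5 for both arms alike: "Final examination in a participating hospital".

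The split by arm is in the asterisk note to Table 2: "Measurement of IOP and blood pressure will be performed either during inpatient stay in participating hospitals (CG) or at home". In the IOP and blood pressure rows that asterisk stands at T1 only. Under Clinical endpoints, "IOP will be measured on all examinations in participating hospitals and at the local ophthalmology practice", and Table 2 lists IOP at T5.

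**The concern.** A claim that blinding is impossible should reach only as far as its reason. What reveals the arm here is the pressure profile: seven days of self-measurement at home, or an inpatient stay. A year later both arms come to hospital for the same examination, and nothing in the described content requires the person holding the tonometer to know the arm.

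Because the article rules masking out for all personnel, it also rules it out where it is practicable. Analysts who work on pseudonymized data cannot remove a bias already present in the recorded value. In a trial of this size the random error of a mean IOP difference is small, so even a slight systematic shift in how staff read or record pressure could show up as a difference between arms. Follow-up IOP at T2 to T4 is measured in the local practices, where the profile was evaluated and therapy may have been adjusted on it. T5 is therefore the follow-up visit at which masked IOP is most achievable.

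**Working it through.** **1. Does the stated reason cover each group of people?**

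| Who | Visit | Must they know the arm? | Source |
|---|---|---|---|
| Patients | all | yes, they do the self-tonometry or are admitted | Intervention; Table 2 |
| Staff who train patients or run the profile | T0/T1 | yes | Intervention; Table 2 legend |
| Treating ophthalmologists | T1 to T4 | yes, they evaluate the profile and may adjust therapy | Intervention |
| Hospital staff measuring IOP | T5 | nothing described requires it | Intervention; Table 2 |

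The T5 content repeats the initial examination, the asterisk for arm-specific measurement is absent at T5, and the interview comes at the end. The measurements can therefore be finished before any discussion that reveals the arm.

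**2. Could T5 staff see the arm?** All measured values go into the electronic case file (Intervention), and hospitals have access to it (Data management and monitoring). A seven-day home record or an inpatient profile identifies the arm. No restricted view is described. That T5 staff would look is an inference; the article does not say so.

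**3. The plan's own sample size, to fix the number per arm.** Inputs from the Sample size section: 20% in both groups, margin 0.05, α = 0.05 (taken as one-sided), power 0.8.

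n = 2 × 0.20 × 0.80 × (1.645 + 0.842)² / 0.05² = 791.4, so 792 per arm and 1584 in total. With 20% drop-out, 1584 / 0.8 = 1980. Both stated figures reproduce. Masking at T5 changes none of them.

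**4. Illustration of sensitivity.** Assumptions, not in the documents: SD of T5 IOP 3 to 5 mmHg, and a net observer shift b in one direction. From the documents: 792 per arm. The test is taken as two-sided at 5%, in line with the 95% confidence intervals named under Statistical analyses.

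SE = SD × √(2/792). With a true difference of zero, the probability of a significant result is Φ(−1.96 + b/SE) + Φ(−1.96 − b/SE).

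| Assumed SD (mmHg) | SE (mmHg) | b = 0 | b = 0.25 mmHg | b = 0.5 mmHg |
|---|---|---|---|---|
| 3 | 0.151 | 5% | 38% | 91% |
| 4 | 0.201 | 5% | 24% | 70% |
| 5 | 0.251 | 5% | 17% | 51% |

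The spread between the last two columns shows how far the result depends on the assumed shift.

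**The case against.** The trial is openly declared unblinded, and the article gives its reason. It nowhere says that T5 staff will know the arm, and rosters and case-file views are details an article usually leaves to the full protocol. That would answer a complaint of missing detail. It does not answer this point, because the article does state something: that personnel cannot be blinded, for a reason that does not reach T5.

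Several limits stand.

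- The tonometer at T5 is not named. Rebound tonometry or Goldmann applanation is specified only for the control group's profile. If the device calculates the value, the room for observer influence is smaller.
- A reader might infer that all T5 outcomes are exposed. The documents do not support this: visual field indices come from automated perimetry, and the EQ-5D is answered by the patient. Staff-measured IOP is the clear case.
- A reader might infer that the non-inferiority conclusion is at risk. It is not: the primary endpoint comes from the pressure profile around T1, which cannot be masked in this way.
- A reader might take the percentages above as expected error rates. They are not. SD and shift are both assumed, a net shift in one direction across several hospitals is required, and the article does not specify a comparison of mean T5 IOP.
- A reader might conclude that T5 IOP should outrank the T2 to T4 values. That is a choice of endpoint hierarchy for the analysis plan, which is not shown.
- The visit has a care purpose, since the article expects a review of disease and medication at the final examination. Masking must not withhold the T1 data from that review. It is also held at the hospital where the patient was trained or admitted, so some patients will be recognised.

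**Conclusion.** The point holds in a limited form. The statement in the Randomization section is broader than its reason, and it leaves staff-measured T5 IOP, one secondary clinical endpoint, open to observer bias that could be reduced at little cost. Exposure is greatest if an operator-read tonometer is used. The primary endpoint, the sample size and the non-inferiority conclusion are untouched.

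The size of any bias cannot be derived from the documents. The rise from 5% to about 17 to 38% illustrates only how little systematic error is needed at 792 per arm. It rests on the assumed SD of 3 to 5 mmHg and the assumed shift of 0.25 mmHg. That T5 staff can be kept unaware of the arm is a design inference from the identical examination in both arms.

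**What to change.** In the Randomization section, limit the statement that blinding is not possible to patients, treating ophthalmologists, and staff who train patients or run the T1 profile. If the sponsor considers masking at T5 infeasible, it should give the specific reason.

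Add to the description of the final examination that:

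- IOP and perimetry are measured and recorded before the arm and the T1 data are opened in the electronic case file, and before the final interview;
- where rosters allow, this is done by existing hospital staff who took no part in that patient's T1 episode;
- the T1 data are available afterwards for the review and the interview.

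The cost is an ordering rule for the visit, with a line in the hospital instructions and, if wanted, a setting in the case file. No visit or post is added. The drawback is incomplete masking, because some patients will disclose their arm or be remembered at the same hospital.

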### Primary endpoint

The primary endpoint is the percentage of detected IOP peak values. Fluctuations and peak values of IOP are considered as a patient-relevant outcome that can be associated with glaucoma progression and warrant adjustment of therapy [15–18].

In the IG, the primary endpoint will be measured by the patients themselves for each eye using an IcareHOME® self-tonometer at six predefined times (6 a.m., 8 a.m., 12 a.m., 4 p.m., 8 p.m. and 12 p.m.) for 7 days (see Table 2). The measurements at 6 a.m. and 12 p.m. will count as night measurements. The night measurements are performed in sitting position, preferably without standing up before. The exact time is recorded electronically. One measurement sequence is based on six individual readings. The IcareHOME® devices calculates the final IOP measurement by discarding the highest and lowest readings and only displaying the mean of the remaining four readings [19]. In the CG, clinical staff will measure the IOP of the patients over at least 24 h at the same times of day and night using rebound tonometry or GAT. To compare these measurements with the IcareHOME®, six readings will be obtained for each eye and the mean of these values will be used for analysis, after discarding the highest and lowest readings.

**Table 2 Tab2:** Study endpoints

Study endpoints	Instruments	Time of assessment						
		*T*_−1_	*T*_0_	*T*_1_	*T*_2_	*T*_3_	*T*_4_	*T*_5_
Patient-related endpoints								
Health-related quality of life	EQ-5D questionnaire		X					X
Clinical endpoints								
IOP fluctuation and peak values	Outpatient/inpatient IOP monitoring	X	X	X*	X	X	X	X
VFI	Standard automated perimetry		X				X	X
MD	Standard automated perimetry		X				X	X
PSD	Standard automated perimetry		X				X	X
Retinal nerve fiber layer thickness	OCT/HRT		X					X
Rim volume	OCT/HRT		X					X
Rim area	OCT/HRT		X					X
Blood pressure (RR)	24 h blood pressure measurement			X*				
Economic endpoints								
Resource utilization (outpatient and inpatient)	Service providers/statutory health insurers	12-month course						
Costs	Service providers/statutory health insurers	12-month course						
Days of incapacity to work (unspecific and diagnosis-specific)	Surveys/statutory health insurers	12-month course						
Sick pay days	Surveys/statutory health insurers	12-month course						
Formative assessment								
Implementation-promoting and inhibiting factors	Interviews, questionnaire	During or at end of project						

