### Data management and monitoring

The ECF has been developed for collecting and managing the patient’s primary data that can be accessed by the local ophthalmologists, hospitals, and the study participants. The eye hospitals will be responsible for the care of their regionally assigned patients. As stated above, the patients will be automatically randomized and patient-specific informed consents will be created by the system.

At predefined points in time, the primary data collected in the ECF and secondary data provided by the participating health insurance companies, both required for evaluation of the study, will be transmitted end-to-end in encrypted form to the trust center at Bielefeld University, which will act independently from the evaluating center. The data will then be pseudonymized, merged, and forwarded to the evaluating center.

For quality assurance, monitoring and grading of images and data will be necessary and will require evaluation by several physicians at a reading center. Typically, one physician will act as junior reader and the other as senior reader to uphold the four-eye principle. In case of doubt, reader A and reader B can each serve as junior reader. In the SALUS project, a glaucoma specialist and a senior resident will be responsible for the grading of diagnostics. During grading, the OCT and HRT images (if available) from the initial and final examination after 12 months will be evaluated with regard to the required outcome parameters (RNFL, BMO-MRW) for each patient group. In addition, the completeness and plausibility of further examination results from the hospital and from the participating local ophthalmologist (IOP, blood pressure, perimetry) will be checked.

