### Statistical analyses

All statistical analyses will be performed using the current version of R/Rstudio and results will be presented following the CONSORT recommendations [36, 37]. Baseline characteristics (including sociodemographic and clinical data) will be analyzed using appropriate descriptive methods. These will include absolute and relative frequency distributions and measures of dispersion, such as median, mean, quantile, variance or standard deviation, used as appropriate, and visualized in a suitable form (e.g., boxplot or histogram). More precisely, baseline characteristics will be summarized for the IG and CG. Standard deviation (when assuming a Gaussian distribution), median, and interquartile ranges will be applied for continuous data (e.g., VFI or blood pressure) and frequencies or percentages will be used for binary data. After analyzing the entire cohort, subgroup analyses will be conducted to determine potential effect modifications (e.g., time effects, age or gender) on the primary endpoint.

The primary endpoint, percentage of detected peak values in IOP, will be analyzed using suitable inferential statistic methods (e.g., Mann–Whitney-*U* test for independent samples and assuming a normal distribution or odds ratios for binary outcomes). An appropriate regression model will be used to evaluate which regressor has an influence on the primary endpoint and residual analysis will be applied to test the results of the model for significance. Secondary endpoints will be evaluated using a similar analysis strategy while using appropriate models for the outcomes.

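### Pseudonymizing the evaluators' data set masks patient identity, not treatment group, so the mechanism the article names cannot by itself blind them to arm

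*Protocol article*

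**What the plan says.** The Randomization section describes an open trial, in which "it will not be possible to blind either the patients, the personnel conducting the study or the healthcare providers". It then makes one blinding claim: "The independent evaluators of the study will be blinded during the study by being provided solely with a pseudonymized data set for data analysis". The wording makes pseudonymization the means of blinding.

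Data management and monitoring gives the matching data flow. Two sources are sent to a trust center that is independent of the evaluating center: "the primary data collected in the ECF and secondary data provided by the participating health insurance companies, both required for evaluation of the study". The next step reads: "The data will then be pseudonymized, merged, and forwarded to the evaluating center". Neither section mentions a coded arm label or the withholding of variables that reveal the arm.

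Other sections show how the data differ between arms:

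- **Primary endpoint.** Patients in the intervention group (IG) measure themselves "at six predefined times (6 a.m., 8 a.m., 12 a.m., 4 p.m., 8 p.m. and 12 p.m.) for 7 days". For the control group (CG): "In the CG, clinical staff will measure the IOP of the patients over at least 24 h". Staff use rebound tonometry or Goldmann applanation tonometry.
- **Time stamps under Table 2.** T1 is a hospital admission in the CG and a consultation with the local ophthalmologist in the IG.
- **Health economic endpoints.** The insurer data cover inpatient and outpatient care in both groups.
- **Statistical analyses.** Patients are analysed in the group to which they were randomized, whichever method they used.

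**The concern.** Pseudonymization and blinding to arm protect different things. The first stops the analyst from learning who a patient is. The second stops the analyst from learning which treatment a patient was assigned. The article offers the first as if it produced the second. A fuller protocol or an analysis plan could add a masking step, but the sentence as printed would still name the wrong mechanism.

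Masking matters to the extent that analysis choices are still open when the data arrive. On the primary endpoint the article says only that it "will be analyzed using suitable inferential statistic methods", with a rank test and odds ratios as examples. If choices such as the test, the treatment of incomplete profiles or the derivation of a peak were made after transfer, they could be made with knowledge of the arm. Readers would meanwhile credit the trial with a blinded evaluation that the described process does not secure.

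**Working it through.** **1. Does the named mechanism mask the arm?** The means named in Randomization is a pseudonymized data set. The steps named in Data management and monitoring are pseudonymizing, merging and forwarding. None of these acts on treatment group. Analysis by randomized group (Statistical analyses) also requires at least a group code in the file. Whether that code is masked is not stated.

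**2. Would a masked code be enough on its own?** Scheduled sequences per eye = times per day × days.

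| Group | Source | Calculation | Sequences per eye |
|---|---|---|---|
| IG | Primary endpoint | 6 × 7 | 42 |
| CG | Primary endpoint, 24-h minimum | 6 × 1 | 6 |
| CG | Introduction, 3-hourly over 24 h | 24 / 3 | 8 |

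The ratio is 42 / 6 = 7 on the Primary endpoint wording and 42 / 8 = 5.25 on the Introduction wording. The two CG schedules differ and must be reconciled, but the conclusion here is the same under either.

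Two limits apply to these counts. The CG period is a minimum, so a two-day stay on the six-times schedule would give 6 × 2 = 12 sequences, still well short of 42. In the other direction, an IG patient who recorded a single day would have 6 and would look like a CG patient. Complete profiles separate the groups; some individual patients could be ambiguous.

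**3. Are there other markers?** The operator differs (patient or clinical staff), and the instrument may differ. The T1 event differs: admission in the CG, outpatient consultation in the IG. Inpatient care in the insurer data is a further marker, though an imperfect one, because IG patients may have other inpatient episodes during the 12 months.

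**4. What exactly is revealed?** All these features show the method received. Because allocation normally determines the method, they usually show the randomized arm too, but not for patients who did not follow their allocation.

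**5. Does any planned figure depend on this?** No. With 20% in both groups, margin 0.05, one-sided α = 0.05 (sidedness is not stated; this choice reproduces the figure) and power 0.80:

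n = (1.645 + 0.842)² × 2 × 0.20 × 0.80 / 0.05² ≈ 792 per group, so 1584 in total.

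With 20% drop-out, 792 / 0.80 = 990 per group, so 1980 in total. This matches the Sample size section, and blinding does not enter it.

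**The case against.** The strongest reply is that a journal article condenses a longer protocol. It does not list the variables in the evaluators' file, say how arm is coded, or say whether IOP arrives as raw readings or as a derived indicator. That stands. A reader might infer that the evaluators receive labelled, reading-level data before the primary analysis and that no blinding exists. The article does not say so, and the claim has to stop at the insufficiency of the one mechanism it names.

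A reader might also infer that evaluator blinding is the trial's only safeguard. It is not. The randomization sequence is concealed from study staff and held by developers independent of those who conduct and analyse the study. The trust center is independent of the evaluating center, images are graded by two readers, and patients are analysed by randomized group. None of these masks the arm from the analyst, but they are real protections and are unaffected by this point.

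Third, the harm may be small. A peak is defined by a rule, 30% above a target set by the treating ophthalmologist, and is not adjudicated by the evaluators. The open analysis choices may be settled in an analysis plan before data arrive, and their absence from the article is not a fault. This limits the consequence; it does not make the blinding sentence correct.

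Finally, 42 against 6 might suggest that the arm can be read off for virtually every patient. Drop-out (20% is allowed for), incomplete profiles, longer CG stays and departures from allocation all weaken that inference.

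**Conclusion.** The point holds in a limited form. Receiving a pseudonymized data set cannot by itself blind the evaluators to arm. The data described would reveal the method received, and so usually the arm, even behind a coded label: 42 scheduled sequences per eye against about 6 to 8 over 24 h, plus the T1 admission and insurer inpatient data.

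This assumes that reading-level or insurer data reach the evaluators before the primary analysis is fixed, which the article neither states nor excludes. The size of any bias cannot be derived from the document. The point corrects a stated design property. It does not show that the result would be biased, and it leaves allocation concealment and the sample size untouched.

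**What to change.** Use the structure already in place. For the primary analysis, let the trust center send the evaluators three things: a patient-level peak indicator derived by a pre-specified script, the covariates, and a masked A/B arm code. Release the reading-level profiles, the insurer data and the true arm only after the primary analysis code is locked. State this in the Randomization and Data management and monitoring sections.

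The cost is one derivation script, a two-step transfer, and an added task for a trust center now described only as pseudonymizing, merging and forwarding. Data queries and review of missing-data patterns on raw readings would go through the trust center or come later.

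If this is not practicable, replace the blinding claim with a plain statement that the analysts are not blinded to arm, and lock the analysis code before data transfer. That removes the misstatement at almost no cost and leaves little room for choices made with knowledge of the arm.
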